## Abstract

**Background:**

In Switzerland, 20,000 people are hospitalized each year as result of drug related problems (DRPs). The sources of DRPs can be related to patients’ behavior (i.e., wrong administration) or to health processes (i.e., drug-drug interaction). No community pharmacy (CP) service focus on DRPs related to patients’ behavior is currently recognized or remunerated in Switzerland. A medication review with follow up (MRF) has been developed to evaluate prescription and non-prescription medication.

**Objective:**

To evaluate the impact of MRF service for the identification and management DRPs associated to patients’ behavior and to describe pharmaceutical interventions carried out through MRF.

**Methods:**

A pre-post intervention study with a cluster design and one intervention group will be carried out in CPs in the canton of Vaud (Switzerland) for 15 months. Volunteer pharmacists will be trained on the identification and management of DRPs related to patients’ behavior. After training, they will include randomly selected adults taking four or more chronic drugs prescribed for at least three months prior to recruitment. Then, they will conduct three pharmacist-patient face-to-face consultations at 6-month intervals. Tasks will be differentiated by pharmacy technician or pharmacist to triage expired medication or to manage DRPs in a structured manner, respectively. The primary outcome is the identification of DRPs associated to patients’ behavior. Secondary outcomes are to assess patients’ medication knowledge, number of expired medications, interventions carried out by pharmacists and pharmacists’ satisfaction. The study will begin in April 2023 in 19 to 35 pharmacies that will recruit at least 162 patients. A sub analysis will be carried out for patients with 65 years old or over.

**Conclusions:**

The MRF intervention features a training designed for an enhanced evaluation of patient’s behavior towards their medication. The study will allow the assessment and management of DRPs in Swiss CPs with the support of the local health authorities and pharmacist association.

**Trial registration:**

Clinicaltrials.gov NCT05348538.

## Introduction

The early 2000s saw the emergence of new roles for community pharmacists in Switzerland, primarily in order to control rising health care costs [1, 2]. With the implementation of the “fee for service” in 2001, a step forward was taken in the direction of pharmacy services. Since then, it has been amended several times in order to respond to the health care system and patients’ needs [3]. According to the Swiss Federal Council, pharmacists could still take on additional tasks in the field of primary care, as they offer easy access to health advice [4]. Since 2016, the canton of Vaud (French speaking part of Switzerland) has been supporting the implementation of a shared electronic medication plan concerning medication safety throughout the care process [5]. In this context, new opportunities exist to strengthen the role of the pharmacist in the process of care by sharing information related to the medication plan.

The clinical management of patients’, especially polymedicated patients, goes through the identification and management of drug related problems (DRPs). The Pharmaceutical Care Network Europe (PCNE) defines a DRP as "an event or circumstance involving drug therapy that actually or potentially interferes with the expected optimal outcome of medical care" [6]. DRPs have several causes, whether related to the drug and dose selection, drug use process, patient or transfer related, etc. [6]. As an example, it has been estimated that the costs of DRPs such as non-adherence is approximately 125 billion euro per year in the European Union [7]. In Switzerland, each year, it is estimated that 20,000 hospitalizations result from DRPs [4]. Identification and management of DRPs related to health process such as drug-drug interactions, contraindications or abuse control are already remunerated as part of the "fee for services" related to prescription validation in Swiss community pharmacies (CPs) [8]. Nevertheless, DRPs related to the patient and his behavior, intentional or non-intentional, (i.e., patient stores drug inappropriately, administers/uses the drug in a wrong way, etc.) need a deeper understanding of the patient’s specific situation and no service related to this aspect is currently available in Switzerland. For example, a treatment intake error could occur due to an instruction that is misunderstood / forgotten or due to improper medication storage at home. One way to identify and prevent the occurrence of DRPs in a structured manner is to conduct a medication review with the patient [9].

Medication review has been defined by the PCNE as "a structured evaluation of the patient’s medications with the goal of optimizing their use and improving health status", which involves the detection of DRPs and the recommendation of interventions [10]. In addition, to increase patients’ safety, a medication review should include both, prescription and non-prescription medication, all of them reviewed by health professionals such as pharmacists for the identification of DRPs. Including non-prescription medication allows pharmacists to ensure responsible use of non-prescription medication [11, 12]. Indeed, community pharmacists are in a privileged position [13] to have an overview of all the medicines taken by patients (prescription and non-prescription) [14–16].

When prescribing, it is important that prescribers are aware of all medications, including non-prescription, in order to prevent interactions or to identify possible side effects: so, it is essential to support actions that allow pharmacists to share the information gathered through a medication review. It could be reach though the implementation of a shared electronic medication plan. Hence, it is important to develop a service that allows the inclusion of the most accurate information on all the medications a patient is taking on such a shared patient’s medication plan.

The Cantonal Health Authorities of Vaud in collaboration with the Cantonal pharmacists association and the Center for Primary Care and Public Health of the University of Lausanne (Unisanté) developed an initiative for a medication review type 2A [17] with follow up (MRF) service. MRF includes follow up due to the results found in the literature, which suggests that medication review with follow up reduces patients’ problems related with the use of medicines [18]. The aim of such service is to perform a medication review at the CP to 1) prevent, identify and manage DRPs related to patients due to the lack of such service in Switzerland, 2) improve patients’ knowledge about their treatments and 3) remove of expired medications for proper elimination by the CPs. Based on the principles of the “brown bag” [19–21] and medication review with follow up [18, 22], MRF includes all the treatments consumed by the patient (prescription and non-prescription medication). This service allows the pharmacists going further than usual prescription validation in terms of detection of DRPs and pharmaceutical interventions. MRF offers the opportunity for the identification and management of DRPs related to patients, the assessment of all medication, disposal of expired medications and the detection of patients’ lack of knowledge about their treatments. For this, the patient brings the medication to the CP before performing the service. MRF also strengthens the role of pharmacy technicians to perform an initial sorting of the medication brought to the CP to divide prescription and non-prescription and to eliminate expired medication. Therefore, allowing pharmacists an optimal use of the time devoted to the consultation. The service is in line with the national objective to reinforce pharmacy technicians’ role, their education and to allow them to assist (under supervision) some services [23].

This paper describes a research protocol that aims to evaluate the impact of the MRF service for the identification and management of DRPs associated to patients’ behavior in CP in Switzerland. This study also aims to describe pharmaceutical interventions carried out through MRF.

## Materials and methods

### Study design and setting

A pre-post intervention study with a cluster design and one intervention group will be carried out in Swiss CPs in the canton of Vaud. The study is taking place for 15 months between April 2023 and June 2024 and it will follow the standard protocol items SPIRIT [24] (see Fig 1 and S1 Appendix).

**Fig 1 pone.0292037.g001:**
[figure not shown]
Spirit schedule of enrollment, intervention and assessments [24].

### Recruitment of study participants

Participant recruitment will take place at two different levels:

**CP and pharmacist level**: the Cantonal Health Authorities and the Cantonal pharmacists association will provide every CP in the canton of Vaud with written study information via email. In order to participate, CPs must have a consultation room and employ at least one pharmacist who will complete the training and will include at least one patient in the study. A CP may have different pharmacists who participate in the study; for those cases, all of them should complete the training and they have to choose a champion pharmacist [25] as a contact person with the research team. A pharmacist who works in different participating pharmacies will be assigned to the CP where he/she works higher number of hours per week.

**Patient level**: patients will be recruited in the participant pharmacies (inclusion and exclusion criteria are listed below). To avoid selection bias by pharmacists selecting patients with more or less DRPs, pharmacists will list all patients who meet the inclusion criteria in each CP (S2 Appendix) and a member of the research team will pre-select 50 of them by using a sequence of computer-generated random numbers to be contacted by champion pharmacists. Pharmacists will follow the order in the list of the 50 randomly pre-selected patients to enroll from one up to ten. Flyers have been designed to help enrolling patients.

Eligible patients will be those adults taking four or more chronic drugs prescribed for at least three months prior to recruitment, irrespectively of the number of non-prescription medications. Exclusion criteria includes: patients suffering from dementia, psychiatric disorder, or other health condition that hinders obtaining informed consent and/or conducting the consultation with the pharmacist; patients who received a medication review within the last six months prior their study enrollment; patients who disagree meeting the pharmacist three times during the study with 6-month interval; patients who are not able to bring all their medication to the CP; patients who cannot speak and read French; patients who does not allow the pharmacist contacting the general medical practitioner (GP) to inform him/her about possible DRPs or patients who will not consent of participating in the study (patients who will not consent to participate will be able of accessing the service without being included in the study).

Eligible patients should meet inclusion criteria at the time of the first pharmacist-patient consultation. After the first consultation, those patients that have any treatment change and inclusion criteria is no longer met, can still be included in the study for the second and third consultation.

### Description of the intervention

The intervention is described using the TIDieR checklist [26] (S3 Appendix). MRF service will involve an intermediate medication review (type 2A as it is based on medication history and patient information) [17] with three pharmacist-patient face-to-face consultations in the CP consultation room at three stages of the study at 6-month intervals. Each of those three consultations will involve three stages: before, during and after the pharmacist-patient consultation. Different tasks performed by the pharmacist or pharmacy technician are also differentiated.

To ameliorate the delivery of the intervention and before the recruitment of patients, participating pharmacists will attend a half-day (four hours) training that will cover service provision, good practice standards, writing reports to patients and other health professionals, data collection and study protocol. The training will include a combination of lecture presentations and interactive sessions including role-play scenarios. The training will be accredited for pharmacists’ continuing professional development and evaluated according to current standards. After the training, pharmacists in each participant CP will inform and train pharmacy technicians for their tasks using an online version of the training about the service and data collection (two online versions will be available, for pharmacists and pharmacy technicians). There will also have a web page that summarize the information [27]. In addition, participant pharmacists will be followed-up by the research team via telephone at least six times during the study (1st, 2nd, 3rd, 6^th^, 12^th^ and 15th months of the study) to support them through the delivery of the service. Pharmacists will also be able to contact the research team by email throughout the study concerning service provision, data entry, etc. The facilitation process will be explained to pharmacists during the training session to ensure recruitment targets, quality of service provision and fidelity to study protocol are met.

**Before the pharmacist-patient consultation**: the purpose of this step is to prepare the necessary documents and the medication for the pharmacist-patient consultation. Patients will be asked to bring all their medication (prescribed and non-prescribed) to the CP. It will be noted if they have performed a pre-selection of the medication before bringing them to the CP. A pharmacy technician will pre-fill the documents with the patient information (medication plan, S4 Appendix). Pharmacy technicians will also review the medication brought by the patient to divide it in two groups (prescription and non-prescription medication) to identify the prescribed medication currently included in the medication plan and expired medications for the pharmacist-patient consultation. Then, pharmacists must have at least 30 minutes to review the prescription medication and non-prescription medication currently taken by the patient to assess potential DRPs before the consultation.

**During the pharmacist-patient consultation**: the purpose is to systematically identify potential DRPs related to patients’ behavior and discuss all DRPs identified (before and during the consultation) to propose interventions with the patient or the GP to resolve them. Also, during the consultation, the pharmacist will evaluate patients’ knowledge about their medication to improve it, if necessary.

**After the pharmacist-patient consultation**: within a maximum of two working days’ period after the consultation with the patient, pharmacists will send a medication plan to both, patient and GP. Additional information will be sent to the GP in case his/her intervention is needed to solve some detected DRPs.

### Data collection methods

Pharmacists will collect data during their intervention at three time points during the study: at recruitment time, six months later and twelve months after the first encounter. A validated tool will be used for identifying and documenting DRPs, the PharmDISC tool [15] (PharmDISC tool will be used only including the 15 DRPs related to patients’ behavior out of the 24 total DRP). In addition, a questionnaire including seven questions to evaluate patients’ medication knowledge will be used. Pharmacist may choose to complete all documents (medication plan and patients’ medication knowledge questionnaire which are merged in a single document, and, if any DRP is detected, the PharmDISC tool) in paper or electronic version during each consultation with the patient.

Participant pharmacists must complete a sociodemographic questionnaire about CP characteristics and his/her individual characteristics during the educational training. This questionnaire on paper will be collected at the end of the study. In addition, pharmacists should complete an electronic anonymous satisfaction questionnaire after each pharmacist-patient consultation. The time taken per patient to deliver the intervention (differentiated between pharmacist and pharmacy technician time) will be recorded. After coding data, champion pharmacists will send a copy of the data collected to the research team within one month after each consultation and/or contacting the GP when necessary. The research team will evaluate the documents to ensure quality of service provision and fidelity to the study protocol. Pharmacists will receive a remuneration of CHF 100 per pharmacist-patient consultation (which cannot be financed by the basic health insurance) and an additional amount of CHF 10 for the additional time spent on documentation of consultations and interventions for research purposes according to the guidelines given in the educational training. The amount of CHF 100 was calculated by the time expected for each professional involved in the service: approximately 45 minutes for pharmacists (CHF 87 per hour) and approximately 45 minutes for pharmacy technicians (CHF 53 per hour).

It is planned that a short communication will be done by the Cantonal Health Authorities; in addition, pharmacists will have flyers (with logo from the Cantonal Health Authorities) to give to patients that will reinforce the message related to the intervention. There will be also a communication from the pharmacists’ association that will go to the GPs association.

### Study measurements and outcomes

Dependent study outcomes and variables are presented in Table 1. In addition, independent variables will be collected in relation to patients (socio-demographic characteristics variables: gender, year of birth and education level and treatment variables: brand name/DCI, dose, formulation, posology for each medicament); pharmacists (socio-demographic characteristics: gender and year of birth and academic and work-related characteristics: role (manager/not manager), year of graduation in pharmacy, place of graduation in pharmacy, working hours in the CP) and CPs (average prescriptions per day, opening hours, location (urban/suburban/rural/industrial area), number of pharmacy technicians and pharmacists employed).

**Table 1 pone.0292037.t001:** Study outcomes.

Primary outcomes (type of variable)	Definition and assessment	Time point
Number of DRPs detected (quantitative)	DRPs associated with patients’ behavior detected by the pharmacist before the consultation (evaluation of the medication) and during the consultation (evaluation of patients’ information). Total number of DRPs and mean per patient and depending on the number of the patients’ medication will be calculated.	Pharmacists will complete the medication plan and PharmDISC tool before and during the consultation.
Evolution on the number of DRPs (quantitative)	Evolution on the number of DRPs associated with patients’ behavior detected will be assessed by comparing the differences between the three consultations with the patient.	Research team will calculate the differences using the medication plan at each consultation.
DRP classification (qualitative)	PharmDISC tool will be used for DRP related classification (15 DRPs related to patients’ behavior out of the 24 total DRP included in the tool): 1. Drug choice: duplicate, accumulation, adverse event. 2. Dose choice: under dose/overdose. 3. Drug use: a. inappropriate timing or frequency of administration, b. inappropriate use method, c. inappropriate treatment duration. 4. Patient: insufficient adherence, insufficient knowledge, burden due to therapy, inappropriate stockage, absence of label. 5. Logistics: prescribed drug not available, error in medication process. 6. Other (to be detailed by the pharmacist).	Pharmacists will complete the PharmDISC tool before and during the consultation.
Number of pharmaceutical interventions (quantitative)	Number of interventions carried out by the pharmacist to correct DRPs and/or prevent their consequence. Total number of interventions and mean per pharmacist, per patient, per number of medications and number of DRPs identified will be calculated.	Pharmacists will complete the PharmDISC tool before and during the consultation.
Pharmaceutical interventions classification (qualitative)	Classification of interventions will be made using PharmDISC tool: • Substitution • Dose adjustment • Adjustment of the delivery amount (package size, quantity of packages, etc.) • Optimization of administration / Change of administration way • Therapy stopped/no delivery • Therapy started • Counselling of patient • Application/use instruction (training) • Delivery of an adherence aid inclusive counselling • Clarification in the case notes (history) • Information to the GP • Therapy monitoring • -Other	Pharmacists will complete the PharmDISC tool before and during the consultation.
Pharmaceutical interventions acceptance (quantitative)	Pharmaceutical interventions acceptance by the patient or the GP (when proposed to the GP, it will be considered as accepted unless the GP states otherwise). Number and proportion of intervention accepted versus proposed according to the number of medications and the number of DRPs.	Pharmacists will complete the PharmDISC tool during the second and third consultation.
**Secondary outcomes**	**Definition and assessment**	**Time point**
Number of removed medications (quantitative)	Expired or in bad condition or unused medications will be identified after reviewing the medication brought by the patient to the pharmacy: total number, mean per patient and percentage in relation to the total medication brought by the patient will be documented.	Pharmacists will complete the medication plan during the consultation with patients.
Number of removed medications discharged (quantitative)	Number of medications proposed to be removed and accepted by the patient after pharmacist-patient consultation: total number, mean per patient and percentage in relation to the total expired medication identified will be documented.	Pharmacists will complete the medication plan during the consultation.
Patient’s knowledge (quantitative)	Medication knowledge evaluation questionnaire with 7 questions (Why do you take this medication?; When do you take this medication?; How many tablets/pushes/milliliters do you take per dose?; How do you take this medicine with food?; What do you do if you forget to take a dose of this medicine?; What side effects may occur with this medicine?; At home, where do you keep this medicine?). The patient scores 1 point if he/she knows the correct answer, 0 points if he/she does not know and -1 if the information given is incorrect. Score goes from -7 (patient who answers all questions incorrectly) to 7 (patient who answer all questions correctly) for each medication that the patient is taking. A score of 0 has no particular significance, apart from being in the middle of the two extremes. The questionnaire is being validated nowadays in a separate project. It aims to evaluate patient’s knowledge over time, rather to differentiate between patients. The total score and the mean score (total score divided by the number of medicines) will be documented.	Pharmacists will complete the questionnaire during the consultation (included in the medication plan).
Pharmacists’ satisfaction (qualitative)	Pharmacists’ satisfaction with MRF will be measured using a questionnaire submitted (8 questions using a Likert scale from "Totally disagree" to "Completely agree"). Once received by the research team, all questionnaires will be coded.	Pharmacists will complete after the first pharmacist-patient consultation and at the end of the study.
**Other outcomes**	**Definition and assessment**	**Time point**
Participation (quantitative)	In order to test the interest and feasibility of the service, participation rate will be calculated as the number of patients who accepted to participate in the study of those who were proposed to participate in the study after randomly pre-select patients who meet the inclusion criteria. The reasons for refusal will also be documented.	Pharmacists and pharmacy technicians will complete an inclusion document at the beginning of the study, listing all patients in the pharmacy following the inclusion criteria.
Service duration (quantitative)	Time (minutes) invested by the pharmacists and the pharmacy technicians to deliver the intervention (recorded separately). Time invested at each consultation and total duration will be considered.	Pharmacy technicians (before the consultation) and pharmacists (after the consultation) will complete the medication plan.
DRP severity (qualitative)	Severity categorization of pharmacists’ evaluation following SCOPE criteria. Severity can be classified as mild (I, II), moderate (III, IV) and severe (V and VI).	Research team will categorize the severity of DRPs using the PharmDISC tool completed by the pharmacist at the consultation.

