### Statistical methods and analysis

Continuous variables will be summarized using mean and standard deviation, or median and percentiles depending on the distribution of the variable. To assess normality, the Kolmogorov Smirnov test will be used. Categorical variables will be reported by frequency and proportion. For the comparison of continuous variables, the T Student’s test or the ANOVA test will be carried out if there is a normal distribution, and Kruskal-Wallis otherwise. The comparison of the categorical variables will be carried out using the χ2 test, the Fisher’s exact test or Yate’s chi-squared test if necessary.

For each patient, differences between consultations (second and first consultations, third and first consultations) will be compared for dependent variables (number of DRPs and medication expired, patient knowledge score, pharmaceutical interventions and medication removed, proportion of pharmaceutical interventions acceptance). A linear regression model will be performed accounting for the cluster effect. A cluster effect is expected by the way pharmacists interact with their team and the surrounding GPs, this could influence the number and type of DRPs detected and interventions made. A sub analysis will be carried out to evaluate the effect of patients undertaking or not a pre-selection of their medication before attending the pharmacy. Firstly, variables will be considered significant (p-value<0.2) in a bivariate model to be included in a multivariate model. Secondly, the variables considered significant at a value of p<0.1 in the multivariate model will be included in the final model. The level of significance will be set at p<0.05; the software STATA 17® will be used. An analysis with completed cases will be made (patients with data for the three consultations). In addition, an analysis with the whole sample will be made where, for the management of missing data, initial value will be considered as not been modified (baseline observation carried forward-BOCF) [28]. In case of a sufficient number of patients who are 65 years old or over are randomly included in the study, a sub analysis will be carried out to target the intervention to a specific group of patients with higher risk for DRPs [29, 30].

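### Acceptance of interventions counts an unanswered GP proposal as accepted, and it is recorded on two occasions although the planned comparisons need three values

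*Protocol article*

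**What the plan says.** Table 1 (Study measurements and outcomes) lists acceptance of pharmaceutical interventions among the primary outcomes. Acceptance may come from the patient or from the GP, and the summary is "Number and proportion of intervention accepted versus proposed according to the number of medications and the number of DRPs". For proposals sent to the GP the scoring rule is "when proposed to the GP, it will be considered as accepted unless the GP states otherwise".

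The time point for this row is "Pharmacists will complete the PharmDISC tool during the second and third consultation". The rows for the number and the class of interventions have a different one: "Pharmacists will complete the PharmDISC tool before and during the consultation". Interventions can therefore be proposed at all three consultations, while acceptance has two named recording occasions.

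Statistical methods and analysis states that, for each patient, "differences between consultations (second and first consultations, third and first consultations) will be compared for dependent variables". The list of those variables includes "pharmaceutical interventions and medication removed, proportion of pharmaceutical interventions acceptance". The same section plans a complete-case analysis and a whole-sample analysis in which missing values are filled by baseline observation carried forward (BOCF).

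**The concern.** There are two separate problems.

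First, the scoring rule treats missing information as a favourable result. A proposal that the GP never read and one that the GP agreed to receive the same code. The error has one direction, and fewer replies give a higher reported rate. A change in the rate between consultations could then reflect a change in GP reply behaviour alone.

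Second, the two planned differences need an acceptance proportion for the first, second and third consultations, but Table 1 supplies two recordings. The article does not say which consultation's interventions each recording covers, and the third-versus-first difference depends on that.

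At stake is how a listed outcome is interpreted, and one of the two comparisons planned for it.

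**Working it through.** The article states no acceptance rate, GP reply rate or share of interventions sent to the GP, so there is no figure to reproduce. All values of r, q, p and g below are assumptions.

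**1. Effect of the silence rule on the GP rate**

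Let r be the share of GP proposals answered, p the acceptance among answered proposals, and q the true acceptance among unanswered ones.

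- Reported rate = r·p + (1−r)
- True rate = r·p + (1−r)·q
- Overstatement = (1−r)(1−q), which is never negative. It is zero only if every GP replies or every silent GP accepted.

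With q = 0.6:

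- r = 0.3: 0.7 × 0.4 = 0.28, or 28 points
- r = 0.5: 0.5 × 0.4 = 0.20, or 20 points
- r = 0.8: 0.2 × 0.4 = 0.08, or 8 points

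Over a wider range, r = 0.3 with q = 0.3 gives 0.7 × 0.7 = 49 points, and r = 0.8 with q = 0.7 gives 0.2 × 0.3 = 6 points.

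**2. Effect on the overall rate**

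Only GP-directed proposals are touched. If a share g of interventions goes to the GP, the overall overstatement is g(1−r)(1−q). With q = 0.6, in points:

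| g | r = 0.3 | r = 0.5 | r = 0.8 |
|---|---|---|---|
| 0.1 | 2.8 | 2.0 | 0.8 |
| 0.3 | 8.4 | 6.0 | 2.4 |
| 0.5 | 14.0 | 10.0 | 4.0 |

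**3. Sensitivity to reply behaviour**

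Take p = q = 0.6, so true acceptance is 60% throughout. The reported rate is 1 − 0.4r, which is 80% at r = 0.5 and 88% at r = 0.3. A fall in replies from 50% to 30% would appear as an 8-point rise in acceptance with no real change.

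**4. Which comparisons the two recordings can support**

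| Reading of the Table 1 time point | Consultations with a value | Second vs first | Third vs first |
|---|---|---|---|
| A. Each recording covers the previous consultation's interventions | 1, 2 | computable | not computable |
| B. Each recording covers the same consultation's interventions | 2, 3 | not computable | not computable |
| C. As A, and the third consultation also records its own | 1, 2, 3 | computable | computable, but a same-day value is set against one taken six months later |

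Reading A is the likeliest, because acceptance is usually known only after the proposal and the row omits the first consultation. Data collection is scheduled "at recruitment time, six months later and twelve months after the first encounter", so no patient visit follows the third consultation.

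**5. Carrying the baseline forward**

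Under A and C, the first-consultation value is entered at the second consultation. It exists for patients who attend that visit and is absent for those lost before it. With the planned 15% dropout over the whole study, that is at most about 0.15 × 162 ≈ 24 patients. Under B no patient has a first value.

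**The case against.** The strongest reply is that the article is condensed and the study forms may say which interventions each recording covers. Data Collection Methods also has pharmacists return data "within one month after each consultation and/or contacting the GP when necessary", so a GP reply after the third consultation could be captured. This stands as far as it goes. A reader might infer that acceptance is never recorded for third-consultation interventions, but that is reading A and not the text. It does not rescue the comparison, because Table 1 does not name the one-month return as the acceptance time point, and a value gathered within a month would still differ in follow-up from one gathered at six months.

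Three other strong readings also fail.

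- A reader might conclude that the acceptance rate mostly measures GP non-response. The article gives no GP share, and its intervention list includes counselling, use instruction and adherence aids, to which the rule need not apply.
- With p = 0.6 and r = 0.3, the rule reports 88% while confirmed acceptance is 0.6 × 0.3 = 18%. The gap should not be read as the bias. The 18% treats every silent GP as a refusal, which is the opposite extreme.
- A reader might say that BOCF has no baseline value for anyone. That is so only under reading B.

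The primary status of this outcome is also uncertain. Table 1 places it there, but the Abstract counts pharmacists' interventions among the secondary outcomes, the Discussion speaks of one primary outcome measure, and Sample Size rests on the difference in drug-related problems. This limits the weight of the point but does not remove it.

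**Conclusion.** The point holds in two parts.

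The GP component of acceptance, as defined, is an upper bound. Its excess over the truth is 28, 20 or 8 points at reply rates of 0.3, 0.5 and 0.8 if silent GPs accept at 60%. The excess in the overall rate is smaller, in proportion to the GP share. The direction follows from the stated rule; the size rests on assumptions, because the article gives none of the inputs.

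The Table 1 time point and the planned comparisons do not fit together. Third versus first cannot be computed under readings A and B and is not like for like under C. Second versus first is sound under A. Under A, BOCF lacks a value only for patients lost before the second consultation.

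The result for drug-related problems, on which the trial was sized, is unaffected. The point should be corrected but does not threaten the trial's main comparison.

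**What to change.** - Record each GP proposal as accepted, refused or no reply.
- Report patient and GP acceptance separately.
- Show no reply as its own category for GP proposals, and give two bounds: no reply counted as accepted (the current rule) and as not accepted. Neither bound alone should be the headline rate, since scoring silence as refusal biases the rate downward.
- Use a matching change in the medication plan at the next consultation as evidence of acceptance only for interventions that would show there. It cannot show acceptance of counselling or use training.
- State which consultation's interventions each recording covers.
- Limit the acceptance comparison to interventions from the second versus the first consultation, and remove third versus first for this variable.
- Exclude acceptance from BOCF where no first value exists.

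The cost is one extra code on the form, a short re-briefing of sites and a few changed sentences. The reported rate will be lower or have a wider range. Data collection began in April 2023, so some early records may not show whether the GP replied; these should be counted and reported as such.
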